**Objective:**

The aims of this research protocol are to (1) develop a high-calorie-expenditure training program to cover target calorie expenditure according to the trainability of women classified as overweight (according to a BMI of 25-29.9 kg/m^2^); (2) determine the effect of high-calorie-expenditure workouts on conditioning, glycemic variables, and body composition; and (3) evaluate the implementation of the intervention and results in comparison with outcomes obtained under a standard-calorie-expenditure training program.

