**Results:**

Preliminary results show significant weight loss in both the high- and standard-calorie-expenditure groups (*P*=.003). Significant improvements were also found in muscle percentage (*P*=.05) and BMI (*P*=.05) for the high-calorie-expenditure group. Analyses are ongoing for glycemic indices, inflammation factors, and blood parameters.

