### Outcome Measures

#### Baseline Measures

Before starting the training, the participants undergo a 2-week familiarization period with the physical tests and training protocol. Participants’ anthropometric characteristics such as height, weight, and body composition variables (determined at 220 Hz with the device) are measured prior to randomization.

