## Results

Preliminary results show that the high-calorie-expenditure training program more than doubled weight loss and reduced fat mass, along with a further decrease in waist circumference. Figure 3 shows the changes in the body composition of the three groups. The overall goal of increasing exercise energy consumption was achieved, with an increase in energy consumption in physical activity of more than 3500 calories per week in the high-calorie-expenditure group and up to 1200 calories per week in the standard-calorie-expenditure group. Preliminary statistical analyses indicate significant differences between the stages and in the interaction of time and group. Additional analyses of functional parameters, lipid profiles, inflammatory factors, and blood indicators are ongoing.

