**Figure 3 figure3:**
[figure not shown]
Changes in BMI, weight, fat content, and muscle in the the three groups. CG: control group (no exercise); HC: high-calorie-expenditure group; SC: standard-calorie-expenditure group.

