## Discussion

### Principal Findings

The primary results of this study show that high-calorie-expenditure exercise is superior to regular exercise in terms of achieving weight loss in women with overweight. Our results demonstrate that both types of exercise (high and standard calorie expenditure) led to significant weight loss (*P*=.003). Significant changes were also observed in muscle percentage (*P*=.05) and BMI (*P*=.05) of the high-calorie-expenditure group after 12 weeks. The functional tests also showed that both exercise programs had a positive effect on the participants.

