### Limitations

This study has several limitations. The physical activity levels of the participants obtained with the IPAQ were not installed in the software and mobile phones of each participant. However, the results were determined to be satisfactory after answering the questionnaire. In addition, because this investigation started immediately after the lifting of restrictions related to the COVID-19 pandemic to conform with health protocols, it is possible that this long period of isolation had mental and psychological consequences on the participants.

When developing a target exercise interval, it is important to consider relevant variables to ensure that energy expenditure is at the level necessary for the health of all people. Further research is needed to confirm our results and determine the optimal group-based workouts that maximize caloric burn while increasing adaptation. In this study, we have confirmed the applicability of 5 high-calorie-expenditure training sessions in women over 35 years old, with benefits of weight loss, fat mass reduction, and muscle mass increase. In addition, our initial analyses suggest benefits with respect to inflammation and the lipid profile. However, the effects of these exercises on the immune system, bone conditions, reproduction, and other health facets remain unclear. It will also be valuable to examine the effect of this type of exercise over the longer term for 6 months to 1 year.

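### The Limitations section claims a gain in muscle mass, but the readable text reports only muscle percentage, which can rise through fat loss alone

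*Protocol article*

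**What the plan says.** All references are to the protocol article.

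- **Objective (abstract).** The second aim is to "determine the effect of high-calorie-expenditure workouts on conditioning, glycemic variables, and body composition". Muscle mass is not named.
- **Baseline Measures.** The measurements include "body composition variables (determined at 220 Hz with the device". Neither the muscle variable nor its unit is defined.
- **Abstract, Results.** For the high-expenditure group: "Significant improvements were also found in muscle percentage", with P=.05.
- **Principal Findings.** For the same group after 12 weeks: "Significant changes were also observed in muscle percentage", again with P=.05. The same paragraph says that "both types of exercise (high and standard calorie expenditure) led to significant weight loss" (P=.003).
- **Results.** The high-expenditure program "more than doubled weight loss and reduced fat mass".
- **Figure 3 caption.** "Changes in BMI, weight, fat content, and muscle in the the three groups". The image is not available here, and the caption does not say whether muscle is in kg or percent.
- **Limitations.** The program is described as applicable to women over 35, "with benefits of weight loss, fat mass reduction, and muscle mass increase".

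**The concern.** Between the results and the Limitations section, the quantity changes from a percentage to a mass. The two can move in opposite directions when body weight is falling, and the article reports that body weight fell in both exercise groups. A significant rise in muscle percentage is therefore not evidence of muscle gain.

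A stated benefit of the high-expenditure program is at stake. The Introduction describes this training as a form of caloric restriction and discusses reductions in fat-free mass, so whether muscle is kept is a question the article itself raises. The Conclusion then recommends multimodal methods for weight-loss programs. A reader would take from the Limitations sentence that muscle was built, when the reported result is equally compatible with muscle being unchanged or somewhat reduced.

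**Working it through.** **No reported figure to reproduce.** The article gives P=.05 for muscle percentage without means, standard deviations or kg values, so the result cannot be recomputed. The sample-size calculation plays no part in this point.

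**Definition.** Let M be muscle mass, W body weight, d the weight lost and f the share of that loss that is muscle. I take muscle percentage to be M/W, the usual meaning; the article does not define it.

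- Before: M/W.
- After: (M − f·d)/(W − d).

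**When the percentage rises.** (M − f·d)/(W − d) > M/W gives W·M − W·f·d > W·M − M·d, which reduces to f < M/W. So the percentage rises whenever muscle's share of the lost weight is below its share of baseline body weight. No muscle gain is needed, and up to (M/W)·d kg of muscle can be lost before the percentage falls.

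**Assumed inputs.** The documents give no body weight, baseline muscle percentage or kg lost. I use W = 65-80 kg, M/W = 25-35% and d = 2-6 kg.

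**Pure fat loss (f = 0), no muscle gained:**

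| W (kg) | M/W | d (kg) | Before | After | Rise (points) |
|---|---|---|---|---|---|
| 80 | 25% | 2 | 20/80 = 25.0% | 20/78 = 25.64% | 0.64 (smallest) |
| 72 | 30% | 2 | 21.6/72 = 30.0% | 21.6/70 = 30.86% | 0.86 |
| 72 | 30% | 4 | 21.6/72 = 30.0% | 21.6/68 = 31.76% | 1.76 |
| 65 | 35% | 6 | 22.75/65 = 35.0% | 22.75/59 = 38.56% | 3.56 (largest) |

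**Some muscle lost.** At 72 kg and 30% muscle, a 4 kg loss that includes 0.5 kg of muscle gives (21.6 − 0.5)/68 = 31.0%, still a rise of 1.0 point. Break-even is 0.30 × 4 = 1.2 kg of muscle lost: (21.6 − 1.2)/68 = 30.0%.

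**Dependence on weight lost.** The second and third rows differ only in fat lost, 2 kg against 4 kg, yet the rises differ by 1.76 − 0.86 = 0.90 points with identical muscle mass. The Results section says weight loss was more than doubled in the high-expenditure group. If percentage were compared between groups, this mechanism alone would favour the group that lost more weight.

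**The case against.** The strongest reply is that this is a loose phrase in a Limitations section. Several parts of that reply stand.

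- **Figure 3.** A reader might infer that muscle percentage is the only muscle result in the whole article. The documents do not support that: the Figure 3 panel may show kg. The point is limited to the readable text. If the panel shows a tested gain in kg, the authors need only say so.
- **The objective.** A reader might infer that the body-composition objective as a whole goes unanswered. It does not: weight, BMI, fat mass and waist circumference are also reported. Only the muscle component is affected.
- **Planned analysis.** No section fixes muscle percentage as an endpoint to be compared between groups, and the muscle result is reported for the high-expenditure group only. A kg analysis cannot be presumed absent from the full plan.
- **Strength of the claim.** The article's word for confirmation attaches to the applicability of the sessions, not directly to muscle gain. The preceding sentence asks for further research, and the results are labelled preliminary.
- **Actual muscle loss.** Nothing in the text shows that muscle was lost. The examples show only that the reported result cannot exclude it.

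What does not stand is any suggestion that the sentence is supported as written. The Discussion also mentions increased muscle mass when summarising cited literature on combined exercise, but that is not a finding of this trial.

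**Conclusion.** The point holds as an error of interpretation. On the readable text, an increase in muscle mass is asserted while only muscle percentage is reported, during a period when weight and fat mass fell. The mass claim does not follow from that result.

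The algebraic condition f < M/W needs only the definition of muscle percentage as muscle over body weight. The size rests entirely on assumed values: rises of about 0.6 to 3.6 points with no muscle gained. Whether the observed rise lies inside that range cannot be judged, because the article's text does not give it. Randomization, sample size and measurement schedule are untouched, and the data collected can settle the question.

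**What to change.** 1. For each participant and visit, compute muscle (or fat-free) mass in kg as percentage times body weight at that visit. Do this per participant, not from group means.
2. Analyse the change in kg by group, with a between-group comparison across the three groups. Keep muscle percentage as descriptive.
3. State the unit of the muscle panel in the Figure 3 caption.
4. Unless the kg analysis shows a gain, reword the Limitations sentence to claim an increase in muscle percentage rather than in muscle mass.

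No new data are needed, since muscle percentage and weight are already measured. The cost is one extra analysis and a wording change, and the stated benefit may become less favourable.

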### Conclusion

Multimodal exercises with high calorie expenditure have a significant effect on body composition and glycemic and health indicators, and these exercises can be performed by people who are overweight, including those with type 2 diabetes. Our study only focused on women over 35 years of age with a sedentary lifestyle and a body weight in the overweight range. Future work could focus on the impact of this program on both men and women with obesity and overweight. In addition, tools and machines can be incorporated into the programs in future research. Several studies have shown that multimodal exercises may offer a means of repairing and recharging metabolism for middle-aged people with inactive lifestyles. Training programs using the ACSM’s minimum protocols for exercise have shown significant improvements in strength and endurance. The ACSM guidelines seem appropriate for a large proportion of the adult population who are seeking to gain muscle and lose fat. Research suggests that aerobic and total body exercise may play an important role in fitness and health, particularly with regard to body composition, glucose utilization, resting blood pressure, blood lipid profile, vascular status, and gastrointestinal transport, along with positive impacts on bone mineral density, heart function, back pain, arthritis, depression, metabolic syndrome, cardiovascular disease, and all-cause mortality. Therefore, it is recommended to include multimodal methods in weight loss and health promotion programs.

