### Study Population

The program was designed for women who are classified as overweight (BMI=25-29.9 kg/m^2^) without an athletic background. Participants were recruited as a result of local media coverage related to fitness and health. To be considered eligible for this study, individuals had to be of female sex and aged between 35 and 50 years; informed written consent was required prior to the baseline measures and sample collection. The specific inclusion criteria are listed in Textbox 1.

Exclusion criteria are the onset of menopause during training, disruption of the menstruation cycle, and failure to participate in exercises in more than 30% of the sessions.

Inclusion criteria for study participation.In good health without a history of specific diseasesphysical diseases such as diseases and problems of the joints and bones or any type of physical and orthopedic injury to the extent that it would interfere with the implementation of exercises;endocrine and metabolic diseases (eg, type 1 or type 2 diabetes, kidney and liver thyroid diseases);cardiovascular diseases (eg, high blood pressure, coronary artery disease, atherosclerosis, peripheral vascular disease, heart disease);mental and psychological diseases (eg, depression, schizophrenia, mania);epilepsy;anemia;cancer;any infectious and inflammatory diseases.BMI of 25-29.9 kg/m^2^, leading to a classification of overweight.Inactive; participated in sports/fitness activities less than 3 times a week for less than 20 minutes in the past year and did not participate in organized activities in the past year.Premenopausal with a relatively regular menstrual cycle.Not taking any drugs that affect heart rate, metabolism, and body weight (such as drugs related to diabetes or thyroid diseases), antidepressants, nonsteroidal anti-inflammatory drugs, reproductive hormones, supplements, and vitamins.Have not consumed turmeric, caffeine, or alcohol 48 hours prior to each blood sample collection.Completed and signed the consent and engagement forms as well as medical history forms.

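### The Conclusion claims a significant glycemic effect and suitability for people with type 2 diabetes, but diabetes bars entry to the trial and no glycemic result is reported

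*Protocol article*

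**What the plan says.** The first sentence of the Conclusion makes two claims. The first is about effect: "Multimodal exercises with high calorie expenditure have a significant effect on body composition and glycemic and health indicators". The second is about who can do the programme: "these exercises can be performed by people who are overweight, including those with type 2 diabetes". Neither carries a citation, an estimate or a P value.

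Study Population (inclusion criteria in Textbox 1) asks for good health without a history of listed diseases. The list includes "endocrine and metabolic diseases (eg, type 1 or type 2 diabetes, kidney and liver thyroid diseases". A separate criterion reads "Not taking any drugs that affect heart rate, metabolism, and body weight (such as drugs related to diabetes or thyroid diseases". Having diabetes, or taking drugs for it, therefore makes a woman ineligible.

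On the state of the analyses, the Results paragraph of the Abstract says "Analyses are ongoing for glycemic indices, inflammation factors, and blood parameters". The main Results section says "Additional analyses of functional parameters, lipid profiles, inflammatory factors, and blood indicators are ongoing". The P values given in the Abstract and under Principal Findings are for weight, muscle percentage and BMI only.

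**The concern.** Glycemic change is one of the things the trial set out to measure. It appears in the second aim under Objective and in the planned comparison in the Abstract's Methods. A reader who goes straight to the Conclusion would take that aim as met, with statistical significance, when the article reports nothing that would let anyone check it.

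The diabetes clause adds a problem of population. It offers a feasibility statement for people whom the eligibility criteria keep out. Completing the analyses cannot repair this, because the trial should contain no data on such people. The Conclusion ends by recommending multimodal methods for weight loss and health promotion programmes, so the claim is likely to be read as advice for practice.

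**Working it through.** No arithmetic is needed. The check sets each half of the sentence beside what the rest of the article provides.

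**Suitability for people with type 2 diabetes**

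1. Claim (Conclusion): overweight people with type 2 diabetes can perform the exercises.
2. Who was admitted (Study Population): women aged 35 to 50, overweight, inactive, premenopausal, in good health, with no history of type 1 or type 2 diabetes and not on diabetes drugs.
3. Who was randomized (Sample Size and Group Allocation): 33 women, 11 per arm, of whom 11 were assigned the high-expenditure programme.
4. If the criteria were applied as written, the number with known diabetes should be 0 of 33 overall and 0 of 11 in the high-expenditure arm. The word is *should*. Entry rests on medical history and medication, and the screening described under Ethical Considerations and under Sample Size and Group Allocation names no glucose test, so undiagnosed diabetes is not strictly ruled out. That possibility would not give the trial usable data on people with diabetes.
5. Result: the trial offers no evidence on tolerability, adherence or effect in this group.

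**Significant effect on glycemic indicators**

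| Place in the article | What it says about glycemia |
|---|---|
| Abstract, Results | Analyses still running; no figure |
| Abstract, Conclusions | Greater weight loss may in time lead to better glycemic indices; no claim of significance |
| Results | Blood indicators still being analysed; glycemic indices not named separately |
| Principal Findings | P values for weight, muscle percentage and BMI; none for glycemia |
| Limitations | First signals for inflammation and lipids; glycemia not mentioned |
| Conclusion | Significant effect stated as fact |

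The Conclusion is the only place that asserts a significant glycemic effect. It goes further than the Abstract's own conclusion, and nothing in the results sections supports it. The body-composition part of the same sentence at least has reported P values behind it and is not at issue here. The part about glycemic and health indicators has none.

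**The case against.** The strongest defence is that the sentence is a general remark drawn from the literature. The paragraph does mix the trial with outside work: later sentences begin by referring to several studies or to research, and the section on prior studies mentions guidelines covering obesity and type 2 diabetes. The sentence that follows also restricts the study to sedentary, overweight women over 35.

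This does not rescue it. The sentence is uncited, opens the Conclusion, names the trial's own intervention and leads directly into a statement of what the study covered. It reads as the trial's finding. The guideline passage concerns reaching a baseline level of fitness before high-intensity interval training and does not support this programme in diabetes. The limiting sentence covers sex, age, activity and weight, but does not say that women with diabetes were ineligible.

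A second defence is that this is one sentence of discussion that alters no endpoint, sample size or analysis. That is true, and it is why the correction is cheap. It still changes what the trial may be said to show about one of its aims.

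Some stronger readings are tempting but not supported:

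- *That glycemic outcomes were declared positive before anyone looked at them.* The article says the analyses are ongoing, which does not mean they had not begun. What can be said is that no glycemic result is reported.
- *That the inflammation and lipid statement is also a contradiction.* Limitations says "our initial analyses suggest benefits with respect to inflammation and the lipid profile". That is hedged, and a first look is compatible with unfinished analyses. It needs only to stay labelled preliminary.
- *That the Abstract must be rewritten.* Its conclusion makes no diabetes claim and no claim of a significant glycemic effect.
- *That a safety bound can be calculated from the 11 women in the high-expenditure arm.* The article gives no adverse-event count, and a bound from women without diabetes would say nothing about people with it.

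**Conclusion.** The point holds for the opening sentence of the Conclusion, in both its parts. The claim of suitability in type 2 diabetes concerns people the criteria exclude; 0 of 33 participants should have known diabetes. The claim of a significant glycemic effect has no reported estimate, interval or P value behind it, and the Abstract describes those analyses as unfinished.

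This rests on two assumptions: that the eligibility criteria were applied as written, and that the sentence is meant as a conclusion of this trial, which its position and lack of citation indicate. It is a limit on inference. It takes no position on whether people with diabetes should do this exercise.

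**What to change.** 1. Delete the clause on type 2 diabetes from the Conclusion.
2. Limit the conclusion to the population that could enter: healthy, inactive, premenopausal overweight women aged 35 to 50. Say there that women with a history of diabetes or on diabetes drugs were not eligible.
3. Remove the claim of a significant effect on glycemic and health indicators, or replace it with a statement that glycemic and other blood-based results are preliminary and not yet reported.
4. Keep the inflammation and lipid remark in Limitations labelled as preliminary. It needs no other change.

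The cost is rewording a few sentences of the Conclusion. No data, analysis or design element is affected.

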## Abbreviations

ACSM: American College of Sports Medicine
CR: calorie restriction
CT: circuit training
EAT-26: Eating Attitude Test-26
HDL: high-density lipoprotein
HIIT: high-intensity interval training
IPAQ: International Physical Activity Questionnaire
IPAQ-L: International Physical Activity Questionnaire long form
LDL: low-density lipoprotein
MET: metabolic equivalent
NCD: noncommunicable disease
REE: resting energy expenditure
VAS: visual analog scale
VO_2_ max: maximum oxygen rate
